### Phase IVb: Determining aging biomarkers in 25% of the whole sample (stage 1)

In parallel with the epigenetics analyses performed in stage 1, a set of selected circulating biomarkers will be analyzed on plasma samples from the same population. Based on the outcomes of this phase, a subset of these biomarkers will be chosen as a result of their association with primary and secondary outcomes.

### Phase V: Validation of biomarkers in the entire study population (stage 2)

The biomarkers selected in phases IVa and IVb will be validated on the remaining samples (75%, *n* = 798).

### Phase VI: Association of overall biomarkers with primary and secondary outcomes

All the biomarkers validated in stage 2 will be integrated with the clinical, functional and biological data. Several biostatistical and bioinformatics analyses will be conducted to identify biomarker signatures that are strongly associated with primary and secondary outcomes.

The synergy between (a) detailed information about diagnoses for each individual patient, (b) a Comprehensive Geriatric Assessment (CGA), (c) routine laboratory data, (d) epigenetics data, and (e) plasma protein determination will improve the characterization of patients with MM, including the prognostic value for multiple outcomes such as overall mortality, re-hospitalization, and functional decline.

### Outcome variables

#### Overall mortality

Mortality data include the date, place, and causes of death (when available). Up to 10 years' information on survival status (i.e., dead or alive) will be obtained from the Marche Region's administrative database.

#### CGA

CGA was conducted at admission and discharge using the validated interRAI Minimum Dataset for Acute Care (MDS-AC) (51), encompassing identification information, demographic data, functional state assessment, number and type of diagnoses, and number and type of medications, treatments, and procedures (50). Functional status was evaluated on the basis of several dimensions: the number of impaired basic and instrumental activities of daily living (BADL and IADL) (48, 52, 53) as a measure of functional status; the cognitive performance scale (CPS) as a measure of cognitive function; sensory functioning (hearing and vision); history of falls; pressure sores and skin conditions; pain; delirium, and behavioral changes; nutritional status and oral health; urinary incontinence; and, recent weight loss.

#### Use of healthcare resources

Information regarding hospital admissions (number and duration of hospital stays), additional laboratory tests performed, and the use of care services (e.g., nurse home visits, physiotherapy, home help, social transport, and day care facility) were also collected. Up to 10 years of information on the use of healthcare resources will be obtained from the Marche Region's administrative database.

### Exposure variables

#### Demographics

Age, gender, dwelling information, marital status, previous hospital admissions, and family arrangements.

#### Clinical variables

The objective examination includes blood pressure, heart rate, and anthropometric variables (body mass index, BMI). A thorough clinical history was carefully compiled by trained physicians. Diagnoses were coded using the International Classification of Diseases, 10^th^ Edition (ICD10) (54) and the coding of medications was carried out by means of the Anatomical Therapeutical Chemical Classification System (ATC) (55).

### Epigenetic variables

DNA will be extracted from frozen buffy coat samples using standard methods (Ion AmpliSeq DNA Kit). After analyzing DNA quality and quantity with a Nanodrop Spectrophotometer, the Infinium MethylationEPIC BeadChip Kit (Illumina, San Diego, CA, USA) will be used to determine DNA methylation. The Infinium HD Methylation Assay Protocol Guide combines bisulfite conversion of genomic DNA and whole-genome amplification (WGA) with array-based direct capture and scoring of CpG loci.

### Protein variables

Using an immune-affinity assay (ELISA), plasma samples from the study population will be analyzed for selected circulating proteins such as DHEAS, IL-6, CRP, Cyst-C, A2M, and sRAGE.

### Statistical analysis

Baseline characteristics will be described using standard descriptive methods, such as summary statistics and frequency tables. Parametric and non-parametric statistical approaches (such as contingency table analysis, regression, and analysis of variance) will be used when appropriate.

Data pre-processing will be performed using the R package *minfi* (56) and a DNA methylation level will be summarized for each CpG site by calculating a “*beta*” value ranging from 0 to 100%. CpG probes will be treated as missing if the detection *P*-value > 0.01, and CpG sites with more than 5% missing data will be excluded from the analysis.

Epigenetic age will be calculated by multiplying beta values by the regression weights from Horvath [353 CpG sites (35)], Hannum [71 CpG sites (37)], and Levine [513 CpG sites (38)] to create the respective clocks. Delta age (Δage) will be defined as a simple subtraction of the chronological age from the epigenetic age using all the versions of the clock mentioned previously. In all cohorts, cell count predictions will be estimated from DNA methylation data using the Houseman method (57).

The determinants of overall 10-year survival will be calculated using Cox proportional hazards analysis including Δage as independent variables, and corrected for the following confounders: age, gender, clinical, functional, or biological data. The accuracy of exposure variables in predicting mortality will be estimated using Harrell's C-statistics. The same analyses will be repeated by adding the individual age-associated CpGs (one at once) to the Cox model. A two-stage approach will be adopted to validate individual CpG sites associated with mortality. Initially, all of the more than 850,000 methylation sites analyzed by the Illumina Infinium MethylationEPIC Array will be analyzed in a proportion π_sample_=25% of the study sample in stage 1 (*n* = 272), and the results of stage 1 will be used to select a proportion of these *M* CpG sites (Ω_marker_) for follow-up on the remaining sample in stage 2 (75%, n=798). The parameter Ω_marker_ will be selected on the basis of the corresponding *p*-values within the context of the survival analysis.

The validity of the estimated coefficients will be internally verified using a non-parametric bootstrapping resampling analysis with replacements.

In order to reduce the complexity of MM, a dimensionality reduction approach will be performed by clustering patients into a few groups on the basis of the most frequent diagnoses at baseline for each stratum in order to obtain a classification of patients according to an MM pattern. The risk analysis will be repeated for each MM pattern. The association between the epigenetic clock and MM patterns will be determined by means of a Generalized Linear Model. Multiple adjusted models will be developed to consider each possible covariate that could influence the significance of the results and to identify independent variables linked to primary and secondary outcomes. Survival analysis with Kaplan Meier estimates will be performed to assess and compare survival over time among the clusters (Log-Rank test). Cox proportional hazards models will be used to assess and compare survival-time outcomes in each cluster in the presence of possible confounders. Several network medicine-based approaches will be developed in order to build the Human Interactomes and Disease Networks (58). Finally, we will investigate the additive effect of the epigenetic clock on the predictive ability of MM patterns. Changes in Harrell's C and the categorical Net Reclassification Index (NRI) will be calculated with 1,000 bootstrap samples to estimate the 95% CI. A two-tailed *p*-value of < 0.05 will be considered statistically significant. The Bonferroni correction for multiple comparisons will be applied to control for the risk of false-positive results. Statistical analyses will be conducted using the Stata 15.1 Software Package for Windows (Stata Corp, College Station, TX).

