**Methods:**

This monocentric retrospective observational study was conducted as part of a project funded by the Italian Ministry of Health titled “imProving the pROgnostic value of MultimOrbidity through the inTegration of selected biomarkErs to the comprehensive geRiatric Assessment (PROMOTERA).” This study will examine the methylation levels of thousands of CpG sites and the levels of selected circulating biomarkers in the blood and plasma samples of older hospitalized patients with MM (*n* = 1,070, age ≥ 65 years) recruited by the Reportage Project between 2011 and 2019. Multiple statistical approaches will be utilized to integrate newly measured biomarkers into clinical, demographic, and functional data, thus improving the prediction of mortality for up to 10 years.

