The PROMOTERA study aims to identify promising biomarkers of healthspan and mortality, such as selected circulating proteins and several DNA methylation biomarkers in the plasma and blood samples of hospitalized older patients recruited by the Reportage project (Trial registration number: NCT01397682; July 19, 2011). The Reportage project is (50) an ongoing prospective observational study involving older patients consecutively admitted to acute care wards in INRCA research hospitals located in the Italian cities of Ancona, Fermo, Cosenza, and Casatenovo. The project began in September 2011 with the aim of creating a large data repository on demographics, comprehensive geriatric assessments, clinical and diagnostic information, and molecular and biological data on older adults receiving acute care. This study included patients who were recruited until 2019. Potential participants were screened for eligibility after they were provided with information describing the study. Eligibility criteria included: age ≥ 65 years, admission to one of the INRCA research hospitals, and written informed consent. In the case of a participant's cognitive decline or impaired judgment, a proxy (relative or caregiver) was requested to give their additional consent. The absence of informed consent from the patient or caregiver (50) resulted in the participant's exclusion from the study. Baseline data were collected for each patient within the first 24 h of hospital admission. Baseline data were incorporated into a minimum data set comprising demographic information, multidimensional geriatric assessment data, clinical, biological, and diagnostic information routinely collected during hospitalization, also utilizing the interRAI Acute Care Instrument (51). Moreover, the Reportage dataset contained information on drug intake (prior to admission, during hospitalization, and at discharge) and diagnostic and treatment procedures performed during hospitalization (including information from X-rays, computerized tomography, ultrasounds, electrocardiograms, magnetic resonance imaging, etc.). The multidimensional geriatric assessment was repeated within 24 h prior to discharge. Blood samples were taken within 24 h of admission and stored at −80°C. A separate and detailed data sheet was used to collect data regarding *ad hoc* investigations to identify biological markers.

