### Phase I: Follow-up update

Follow-up information on the date of death will be provided for all Reportage project patients for up to 10 years.

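### Samples banked over 7 to 8 years are assayed later, but neither recruitment year nor storage time is among the confounders listed for the Cox models

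*Protocol article*

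**What the plan says.** The cohort was "recruited by the Reportage Project between 2011 and 2019" (Abstract, Methods). Study design gives the start, "The project began in September 2011", and the sampling rule, "Blood samples were taken within 24 h of admission and stored at −80°C". The laboratory work still lies ahead: "DNA will be extracted from frozen buffy coat samples using standard methods" (Epigenetic variables), and the ELISAs on stored plasma are also in the future tense (Protein variables). The ethics approval is dated 2021.

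Under Statistical analysis, the Cox models for Δage are "corrected for the following confounders: age, gender, clinical, functional, or biological data", and the same analyses are repeated for individual CpGs. A later paragraph of that section promises further adjusted models covering any covariate that might matter, but names none. Recruitment year, storage time and assay batch are not mentioned.

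Stage 1 is a random 25% of the sample (n = 272) and stage 2 the remaining 75% (n = 798). CpGs go forward on their survival p-values, and plasma proteins on their association with outcomes.

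On follow-up, Phase I says: "Follow-up information on the date of death will be provided for all Reportage project patients for up to 10 years". The Phase II selection criteria instead require information to be available from baseline to 10 years.

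**The concern.** Storage time before assay is set almost entirely by the recruitment date. A measured level that changes in the freezer therefore carries a component that reflects when the patient was admitted, not the patient's biology. This has two possible consequences.

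- **Dilution.** The drift acts as measurement error and pulls the hazard ratio towards 1.
- **Confounding.** If mortality or case mix also changed between 2011 and 2019, the drift links the marker to death through calendar time. It can then create, hide or exaggerate an association.

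The planned safeguards do not address this. A random split gives both stages the same spread of recruitment years, so an artefact picked up in stage 1 can repeat in stage 2. Bootstrapping resamples the same structure, and Bonferroni controls chance rather than bias.

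**Working it through.** **Inputs from the protocol article.** Recruitment from September 2011 to 2019, month of closure not given: September 2011 to January 2019 is 7.3 years and to December 2019 is 8.3 years. N = 1,070, two-sided α = 0.05, β = 0.2, hazard ratio 1.23, median survival 6.2 years, 10-year follow-up (Sample size).

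**Reproducing the planned N.** Freedman's formula gives ((1.23 + 1)/(1.23 − 1))² × (1.960 + 0.842)² = 738 deaths. With exponential survival, the 10-year death probability is 1 − 2^(−10/6.2) = 0.673 in the reference group and 1 − 2^(−12.3/6.2) = 0.747 in the other, mean 0.710. Then 738/0.710 is about 1,040, within 3% of 1,070. The match assumes two equal groups and a full 10 years for everyone.

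**Assumptions, because the documents give no figure.** Entry is uniform over the window. Drift is D marker SDs between the oldest and newest sample, linear in recruitment date. Mortality changes by a hazard ratio H between first and last recruits. The true effect is exp(ln 1.23 / 2) = 1.109 per SD, the equivalent of 1.23 between two equal groups.

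**Closed form, equal 10-year follow-up.** A uniform entry date scaled to unit length has variance 1/12, so the observed marker has variance v = 1 + D²/12. Expected deaths are about 0.67 × 1,070 = 717.

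- Dilution: the log hazard ratio shrinks by 1/v, and z = 0.1035 × √(717/v). D = 1 gives v = 1.083, HR 1.100, z = 2.66, power 76%. D = 2 gives v = 1.333, HR 1.081, z = 2.40, power 67%. D = 0 gives z = 2.77, power 79%.
- False association when there is no true effect: the slope is ln H × (D/12)/v. With H = 0.67 (1.5 inverted), D = 1 gives HR 0.970, |z| = 0.86 and 14% rejections. D = 2 gives HR 0.951, |z| = 1.55 and 34%.

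**Simulated Cox models** (n = 1,070, 400 runs per setting, error about 2 points, no recruitment-year term):

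| Setting, 10-year follow-up for all | D = 0 | 0.5 | 1 | 2 |
|---|---|---|---|---|
| No true effect, no trend: rejections | 6% | 5% | 5% | 4% |
| No true effect, H = 0.67: rejections | 5% | 8% | 14% | 32% |
| True effect, no trend: power | 80% | 77% | 77% | 65% |
| True effect, H = 0.67 (opposing): power | 79% | 66% | 44% | 13% |

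With data cut 11.4 years after first entry (follow-up 3.1 to 10 years), the second row becomes 4%, 7%, 11% and 19%, and the first stays at 4 to 6%. A separate set of 3,000 simulated cohorts per setting, with a cut-off at the start of 2023 and H = 1.5, gave 10.0% at D = 1 and 20.6% at D = 2. With D = 0.5 it stayed at 5 to 6%.

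**With a linear recruitment-year term**, rejections under no true effect were about 4 to 6% in every 10-year setting, and power was about 77 to 85%.

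**Price if there is no drift.** Stratifying by year, which uses more information than one covariate, moved the standard error from 0.0421 to 0.0424: 0.0424/0.0421 = 1.007, under 1%.

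**The case against.** **This is an article, and it lists classes of covariate.** A full analysis plan may name storage time, batch and plate layout, and the open-ended promise of further adjusted models leaves room for them. That stands in part: one can say only that the named list omits recruitment year, not that the final model will. But the list is given as the adjustment set, every class in it describes the patient, and the promise commits to nothing.

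**The harm is assumed.** This stands. Nothing in the documents says that any of these proteins, CpGs or clocks drifts at −80°C, or that mortality changed over the window. One drift figure is applied to proteins and methylation alike. At 0.5 SD the false-positive rate is at most about 8%.

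**A reader might infer that storage drift alone can produce a false association, or that unequal follow-up by recruitment year biases the Cox model.** Neither is supported. Drift without a mortality trend left rejections at 4 to 6%, with equal and with unequal follow-up, because the Cox model handles that censoring. It is true that late follow-up rests on the oldest samples, but that describes coverage and is not a bias.

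**The spread itself may be smaller.** If the Phase II criterion is applied literally to survivors, a data cut 11.4 years after first entry would admit only those recruited in the first 11.4 − 10 = 1.4 years. That would conflict with recruitment to 2019, and the article does not resolve it.

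**Stratifying everything would cost too much.** Also fair. Under uniform entry, only about 12 to 13% of the usable pairs for Harrell's C fall within one calendar year, so a within-year C would discard most of the information and change what is measured.

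**Conclusion.** The point holds as a low-cost improvement. Sample age varies by 7.3 to 8.3 years, the listed confounders do not include it, and the two-stage design cannot expose an artefact from it. Drift alone dilutes: power about 77% at 1 SD and 65% at 2 SD, against 80% without drift. A false association needs both drift and a trend by recruitment year: about 10 to 14% rejections at 1 SD and 19 to 32% at 2 SD for a hazard ratio of 1.5 (or its inverse) across the window. A trend opposing a true effect costs more power than drift alone. All these sizes rest on assumed drift, assumed trend, uniform entry and exponential survival. The documents show neither drift nor trend, so they do not establish that any planned result is biased.

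**What to change.** In Statistical analysis, add recruitment year, or storage time at assay, as a covariate in the Cox models for Δage, CpGs and plasma proteins at stage 1, stage 2 and Phase VI, and in the Generalized Linear Models for Δage. Storage time at assay is the more exact choice when the stages are pooled, because stage 2 is assayed after stage 1. Stratification by recruitment year can serve as a sensitivity analysis in the full sample. Keep Harrell's C on all usable pairs.

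Within each stage, place samples from all recruitment years at random across arrays and ELISA plates. This has to be settled before the assays run, because batch that coincides with storage time cannot be separated afterwards. Report each marker against storage time, so that readers can see whether drift occurred.

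Reconcile the 10-year availability criterion in Phase II with recruitment to 2019 in the Abstract and Study design, because the spread in sample age depends on it.

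The cost is a sentence in the plan and a plate-layout rule, using dates that the survival analysis already needs. If there is no drift, the standard error grows by about 1% at most in the full sample, and somewhat more in stage 1 and in small multimorbidity-pattern subgroups.

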### Sample size

The sample size was calculated on the basis of the primary objective (the association between the epigenetic clocks' Δage and mortality). For this reason, we planned to include 1,070 samples of individuals from the Reportage Project. This sample was obtained by setting α = 0.05, β = 0.2, and using a Hazard ratio = 1.23, a 10-year follow-up period, and a median survival time of 6.2 years for patients whose Δage was not expected to increase. This sample size is also in line with other study populations in which the prognostic value of several epigenetic clocks were assessed (36). This sample will enable the detection of significant associations between epigenetic clock Δage and mortality during the 10-year follow-up period.

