One limitation of the study is that the sample size could be smaller than required to detect weak associations between the measured biomarkers and potential modifiers of the association between epigenetic age acceleration and mortality risk during the follow-up period. The sample size was designed on the basis of the primary objective of discovering significant associations between epigenetic clocks' Δage and mortality during the 10-year follow-up period. However, due to the number of potential tested modifiers, the Bonferroni correction for multiple comparisons will be applied to prevent false-positive findings. This study will recommend introducing several biomarkers in clinical settings to improve the prognostic value of MM. However, this translational protocol necessitates several estimation and validation phases. A limitation of the project could be the feasibility of a wide-scale implementation of these biomarkers in clinical practice. Nonetheless, the involvement of the most important stakeholders and companies would make it possible to develop new diagnostic and prognostic experimental procedures.

The absence of information regarding the causes of death of patients who died outside of hospital may also be considered to be another limitation of the study. For this reason, the association analysis on causes of death will only be utilized for descriptive purposes and will not be used in the main analyses in order to eliminate their potential influence on the outcomes.

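### Repeating the mortality model within each multimorbidity pattern cannot show whether the Δage effect differs between patterns, and no interaction test is named

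*Protocol article*

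**What the plan says.** All references are to the protocol article.

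- **Statistical analysis, risk model.** A Cox model relates 10-year survival to Δage, adjusted for age, gender and other data. Accuracy is measured by Harrell's C.
- **Statistical analysis, patterns.** Patients are clustered into a small, unspecified number of groups by their most frequent baseline diagnoses. Then: "The risk analysis will be repeated for each MM pattern". A generalized linear model relates the clock to the patterns. Kaplan-Meier curves, the log-rank test and Cox models compare survival between clusters. Changes in Harrell's C and the net reclassification index show what the clock adds to the patterns.
- **Statistical analysis, threshold.** A two-tailed p-value below 0.05 "will be considered statistically significant", with a Bonferroni correction. The number of tests it covers is not given.
- **Sample size.** The planned number is 1,070, set for a single overall effect. On the error rates the section says: "This sample was obtained by setting α = 0.05, β = 0.2". The effect to be detected is a hazard ratio of 1.23 over 10 years. The reference group is taken to have "a median survival time of 6.2 years for patients whose Δage was not expected to increase".
- **Strengths and limitations.** Three patterns are given as examples (cancer, cardiovascular, neurological), and functional status is named as another basis for grouping. The authors concede that the sample may be too small for weak associations involving "potential modifiers of the association between epigenetic age acceleration and mortality risk during the follow-up period", and say Bonferroni will be applied because of the number of modifiers tested. The form of that test is not stated.

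**The concern.** Whether the clock predicts death differently in different disease patterns is a question about a difference between hazard ratios. A separate Cox analysis in each cluster answers another question: whether the hazard ratio in that cluster differs from 1. None of the other stated analyses fills the gap. The log-rank test compares survival between clusters, the generalized linear model compares Δage between clusters, and the C and reclassification analyses measure what the clock adds overall.

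Each cluster holds only part of a sample that was sized for one overall effect. Some clusters will therefore reach significance and others will not, because of cluster size and chance alone. At stake are secondary statements that the clock is prognostic in one disease pattern and not in another. The primary, whole-cohort test is not affected.

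**Working it through.** **1. Inputs.** From the Sample size section: two-sided α 0.05 (two-tailed per Statistical analysis), power 0.80, HR 1.23, median survival 6.2 years in the reference group, 10 years of follow-up, N = 1,070. Assumed, because not stated: a 1:1 split into raised and not raised Δage, exponential survival, equal patterns with equal death rates, and 3 to 5 patterns. Patterns contain different patients, so their results are treated as independent.

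**2. The plan's own figure.**
- ln 1.23 = 0.207.
- Deaths needed (Schoenfeld): 4 × (1.960 + 0.842)² / 0.207² = 733. Freedman: (2.23/0.23)² × (1.960 + 0.842)² = 738.
- 10-year death probability: 1 − 2^(−10/6.2) = 0.673 in the reference group and 1 − 2^(−12.3/6.2) = 0.747 at HR 1.23; mean 0.710.
- N = 738 / 0.710 = 1,040, which is 2.8% below 1,070. Schoenfeld with the reference-group probability gives 1,090.
- At N = 1,070: 1,070 × 0.710 = 760 deaths and power 81%.

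The planned size is thus reproduced closely as a two-group comparison for one overall effect. Both 733 and 760 deaths are carried forward.

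**3. Power in one of k equal patterns.** p = Φ(0.207 × √(D/k) / 2 − z), where D is total deaths, z = 1.960 unadjusted, and z = 2.394, 2.498 or 2.576 for α = 0.05/k with k = 3, 4 or 5. Example with k = 4 and D = 760: 190 deaths, Φ(1.427 − 1.960) = 0.30.

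**4. Chance of a mixed picture** (at least one pattern significant and at least one not) when HR is 1.23 in every pattern: 1 − p^k − (1 − p)^k. Each cell shows D = 733 / D = 760.

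| k | Power, α = 0.05 | Mixed, α = 0.05 | Power, α = 0.05/k | Mixed, α = 0.05/k |
|---|---|---|---|---|
| 3 | 37% / 38% | 70% / 71% | 22% / 23% | 51% / 53% |
| 4 | 29% / 30% | 74% / 75% | 14% / 14% | 44% / 46% |
| 5 | 24% / 25% | 75% / 76% | 9% / 10% | 39% / 40% |

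**5. What Bonferroni does.** With k = 3 and D = 733, the mixed picture falls to 51%, but no pattern is significant 48% of the time (0.781³) and all three are significant only 1% of the time (0.219³). The correction replaces many mixed pictures with uniformly negative ones. The true state, the same effect in every pattern, almost never appears.

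**6. Sensitivity (733 deaths).**
- Two equal patterns: mixed 50% unadjusted, 48% with Bonferroni.
- Three unequal patterns (50/30/20 to 70/20/10): 71 to 75% unadjusted, 53 to 57% with Bonferroni.
- Bonferroni over three clocks as well as the patterns: 33%, 26% and 21% for k = 3, 4 and 5.
- Four patterns, unadjusted, other true HRs: 33% at 1.10, 49% at 1.15, 86% at 1.30.

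**7. Comparison.** If the hazard ratios are equal, a joint interaction test at 0.05 wrongly declares a difference about 5% of the time, by construction.

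**The case against.** A reader might infer that the plan will judge effect modification by comparing significance across patterns. The text does not say so. It says the analysis is repeated, and stratum-specific estimates are compatible with an interaction test. Effect modification by pattern is not a listed objective either. The limitations section says modifiers are tested and admits limited power, and a fuller plan may specify the test. All of this stands, and it rules out saying that a wrong decision rule has been adopted.

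It is also tempting to give a single figure of about 75% as a property of the plan. The documents do not support that. The figure needs four or more equal patterns (or some unequal three-pattern splits), a true hazard ratio of 1.23, a 1:1 exposure and no multiplicity correction, while the same section applies Bonferroni.

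Two further readings go too far. Clock and pattern are not kept apart everywhere, since the C and reclassification analyses need both in one prediction. And nothing shows that the planned pattern-specific algorithms depend on comparing p-values between clusters.

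What the objection does not remove: separate repetition is the stated by-pattern method, in a section that specifies its other methods in some detail. The authors show interest in modifiers of this association. Conceding low power does not stop chance differences between clusters from being read as real.

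**Conclusion.** The point holds in limited form. The only stated analysis of the Δage-mortality association by MM pattern cannot tell a real difference between patterns from chance. With 3 to 5 equal patterns and a common hazard ratio of 1.23, power per pattern is about 24 to 38% unadjusted. Mixed significance arises about 70 to 76% of the time unadjusted, and about 39 to 53% with Bonferroni over the patterns.

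These figures rest on the assumed number and size of patterns, equal death rates, the 1:1 split and a true hazard ratio of 1.23. The Cox model enters Δage itself, so power on a continuous scale would differ; the 1:1 split is used because it reproduces the planned 1,070. The weakness of the method does not depend on the exact figure. It touches secondary, pattern-specific conclusions only.

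**What to change.** In Statistical analysis, after the sentence on repeating the risk analysis, state that:

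- differences in the Δage effect between MM patterns will be assessed in one Cox model of all patients, with the baseline hazard stratified by pattern and a joint Δage-by-pattern interaction test;
- pattern-specific hazard ratios with confidence intervals will come from that model and be reported as estimates only;
- no pattern-specific effect will be claimed unless the joint test supports it;
- the same applies to functional-status groups.

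If an interaction test is already planned, one sentence naming it settles the point.

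The cost is wording only: no new samples, data or follow-up. The downside is that the interaction test has low power. With four equal patterns of 190 deaths and a 1:1 split, the standard error of each log hazard ratio is 2/√190 = 0.145. For a difference between two patterns it is 0.145 × √2 = 0.205. Two observed hazard ratios would have to differ by a factor of about exp(1.96 × 0.205) = 1.5 for that single contrast to reach 0.05. The plan should therefore add that a non-significant interaction does not show the effects are equal.
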